## **11.6 Study Drug Return and Destruction**

Any partially used study drug should be disposed of/destroyed at the site in accordance with trial guidelines and local biological waste management policies. Unused product should be disposed of/destroyed under the supervision of the site clinical trials pharmacist. Records of return and destruction will be maintained.

## **11.7 Concomitant Care**

All aspects of intensive care will be according to standard critical care guidelines.

### **Mechanical Ventilation**

Ventilation according to the ARDSNetwork ARMA trial, which demonstrated a reduction in mortality using a tidal volume of 6 ml/kg PBW will be the standard of care [9]. Target tidal volumes will be  $\leq 6$  ml/kg PBW to maintain a plateau pressure  $\leq 30$ cmH2O. The recommended Positive End Expiratory Pressure (PEEP) will be based on the ARDSnet ARMA trial [9]. (See appendix 2)

Oxygenation will be titrated aiming for SpO2 of 88%-95% or PaO2 7-10kPa. Permissive hypercapnic respiratory acidosis aiming for a pH  $\geq 7.2$  is recommended.

### **Neuromuscular Blocking Drugs**

Patients in both the intervention and control arm can receive neuromuscular blocking drugs (NMBD) at any stage to ensure patient-ventilator synchrony. This is in keeping with recent evidence that suggests NMBD are of benefit in early hypoxaemic respiratory failure due to ARDS [61].

### **Refractory Hypoxaemia**

If the treating physician is concerned about hypoxaemia, interventions including prone positioning or referral for consideration of extracorporeal membrane oxygenation (ECMO) can be applied in either arm of the trial as per standard care in the UK.

### **Intravenous Fluid and Blood Therapy**

It is recommended that patients will be managed with a conservative fluid balance strategy according to best evidence for patients with hypoxaemic respiratory failure (68). Blood transfusions should be in keeping with the best practice of a restrictive transfusion policy (69).

## **11.8 Management During the Study Drug Infusion**

In keeping with standard care of critically ill patients in ICU, patients will be continuously monitored. Guidelines for the management of events during the study drug Infusion are provided in appendix 3.

## 12 SCHEDULE OF ASSESSMENTS

### 12.1 Schedule of Assessments

All patients recruited to the Phase 1 and Phase 2 of the trial must be evaluated according to the schedule of assessments as outlined in Table 2. Data will be collected at each of the following time points:

**Table 2: Schedule of Assessments**

|                               | Day 0 | Day 1 | Day 2-3 | Day 4 | Day 5-6 | Day 7 | Day 8-13 | Day 14 | Day 15-28 | Day 90 (+/- 14 days) | 1 Year (+/- 30 days) | 2 Year (+/- 30 days) |
|-------------------------------|-------|-------|---------|-------|---------|-------|----------|--------|-----------|----------------------|----------------------|----------------------|
| Eligibility assessment        | X     |       |         |       |         |       |          |        |           |                      |                      |                      |
| Informed consent              | X     |       |         |       |         |       |          |        |           |                      |                      |                      |
| Enrolment/ Randomisation      | X     |       |         |       |         |       |          |        |           |                      |                      |                      |
| Baseline data                 | X     |       |         |       |         |       |          |        |           |                      |                      |                      |
| Daily data                    |       | X     | X       | X     | X       | X     | X        | X      |           |                      |                      |                      |
| Chlorphenamine administration |       | X     |         |       |         |       |          |        |           |                      |                      |                      |
| Study drug administration     |       | X     |         |       |         |       |          |        |           |                      |                      |                      |
| Adverse events                |       | X     | X       | X     | X       | X     | X        | X      | X         | X                    |                      |                      |
| ECHO data**                   | X     |       |         | X     |         |       |          |        |           |                      |                      |                      |
| Blood sampling*               | X     |       |         | X     |         | X     |          | X      |           |                      | X                    | X                    |
| BAL Sampling*                 | X     |       |         | X     |         |       |          |        |           |                      |                      |                      |
| Anti-HLA Ab%                  | X     |       |         |       |         |       |          |        | X         |                      |                      |                      |
| Urine sampling*               | X     |       |         | X     |         | X     |          | X      |           |                      |                      |                      |
| Mortality§                    |       |       |         |       |         |       |          |        | X         | X                    | X                    | X                    |
| Medical Event#                |       |       |         |       |         |       |          |        |           |                      | X                    | X                    |

\*Blood urine and bronchoalveolar lavage (BAL) samples for translational studies will be collected where possible

\*\*Echocardiography data will be obtained where possible.

%Blood for anti-HLA Ab will be collected on day 0 and day 28 only where possible

\$Mortality, including cause of death.

#Any significant medical event

### 12.2 Study Visits and Procedures

#### Day 0 (Baseline)

Baseline data (day 0) is the 24 hours preceding the time of recruitment which is defined as the time of study drug administration. If more than one value is available for this 24-hour period the value closest but prior to the time of study drug administration will be recorded. Day 0 (baseline) data collected will include but is not limited to:

- Patient demographics
- Date of birth, gender, height, weight, PBW
- ICNARC Case Mix Programme (CMP) number or equivalent
- Date and time of ICU admission
- Date/time of onset of mechanical ventilation
- Date/time of consent and enrolment (phase 1) or randomisation (phase 2)
- Aetiology of ARDS
- The Acute Physiology And Chronic Health Evaluation score II (APACHE II)
- First qualifying P/F ratio (including date/time)
- Worst P/F ratio (including date/time)
- Murray Lung Injury Score
- Determinants of the SOFA score
- Temperature
- Ventilation parameters including but not limited to: Mode of ventilation, minute volume, RR, mean airway pressure, plateau pressure, PEEP
- Arterial blood gas including but not limited to FiO2, PaO2, PaCO2, pH, lactate
- Oxygenation Index
- Use of adjunctive therapies
- Renal replacement therapy
- Clinical laboratory assessments: renal, liver function, ferritin and CRP, haematological and coagulation parameters where possible
- Blood for anti-HLA antibodies will be collected where possible
- Echocardiography parameters (during phase 2 study only) including but not limited to ventricular size and function and tricuspid annular plane systolic excursion (TAPSE) will be collected where possible.
- Clinical or PCR diagnosis of COVID-19

Baseline blood, urine and BAL for translational studies will be taken (where possible) prior to study drug administration. Sampling procedures are outlined below.

## Day 1

Day 1 is from the time of recruitment (study drug administration) to the end of that calendar day. If more than one value is available for this period, the value closest but after the time of administration will be recorded. The following data will be recorded:

- Date/time of expiry of the study drug.
- Date/time of commencing the infusion of the study drug.
- Date/time of completion of infusion of the study drug.
- Study drug administration.

The following parameters will be recorded immediately prior to study drug administration and every 15 minutes for the duration of the infusion of study drug and every hour for the next 5 hours.

- FiO2, PEEP, oxygen saturation and plateau pressure as well as arterial blood gas pH, PaO2 and PaCO2 if clinically available.
- Heart rate, systolic and diastolic blood pressure, vasopressor doses.

Temperature will be recorded directly prior to study drug administration and will be recorded every 15 minutes for the duration of the infusion of the study drug and every hour for the next 5 hours.

### **Day 1-14 (Daily Data)**

Daily data for Day 1 should be collected after infusion of the IMP.  $\text{FiO}_2$ ,  $\text{PaO}_2$  and  $\text{PaCO}_2$  will be recorded approximately every 12 hours on Days 2 and 3. All other daily measurements will be recorded and collected between 6-10am or as close to this time as possible, unless otherwise stated in the CRF. Daily data will be collected to day 14, or until ICU discharge, and will include but is not limited to:

- Determinants of the SOFA score
- Temperature
- Ventilation parameters including but not limited to: Mode of ventilation, minute volume, RR, mean airway pressure, plateau pressure, PEEP
- Arterial blood gas including but not limited to  $\text{FiO}_2$ ,  $\text{PaO}_2$ ,  $\text{PaCO}_2$ , pH, lactate
- Use of adjunctive therapies
- Renal replacement therapy
- Clinical laboratory assessments where collected as part of standard care: renal, liver function and CRP, haematological and coagulation parameters where possible.
- Overall fluid balance
- Adverse event assessment
- Echocardiography parameters (during phase 2 study) including but not limited to ventricular size and function and tricuspid annular plane systolic excursion (TAPSE) will be collected where possible (on day 4 only).

### **Day 4, 7 and 14**

- Blood and urine will be taken on days 4, 7 and 14 (where possible). BAL will be taken at day 4 where possible (or the day thereafter when clinically stable)

### **Day 15 - 28**

- Blood for anti-HLA antibodies will be collected on day 28 where possible

### **Day 90**

- Adverse events will be collected up to day 90

### **Year 1**

- Significant medical events
- Blood sample will be taken (where possible)

### **Year 2**

- Significant medical events
- Blood sample will be taken (where possible)

The following data will also be collected:

- Date/time of extubation
- Date/time of re-intubation
- Date/time of discontinuation of mechanical ventilation (unassisted breathing)
- Date/time of critical care discharge
- Date/time of hospital discharge
- Date of death, including cause of death
- Final diagnosis on ICU discharge/death

Extubation is defined as first time being successfully free from an endotracheal tube or a tracheostomy tube for 48hrs.

Unassisted breathing i.e. no ventilatory support is defined as; extubated with supplemental oxygen or room air, or open T-tube breathing, or tracheostomy mask breathing, or CPAP without inspiratory pressure support for 48 hours. Patients receiving pressure support via non-invasive ventilation (except for sleep disordered breathing) or extra-corporeal lung support will be defined as receiving ventilatory support. The 48 hour period to define successful unassisted breathing is not included in the time to unassisted breathing.

Discharge from critical care is defined as first discharge to a ward in the hospital or another hospital; a transfer between ICUs is not considered a discharge from critical care. Hospital discharge is the first date that the patient is discharged to home/community, a transfer between hospitals is not considered as a hospital discharge.

VFDs to day 28 are defined as the number of days from the time of initiating unassisted breathing to day 28 after study drug administration, assuming survival for at least 48 hours after initiating unassisted breathing and continued unassisted breathing to day 28. If a patient returns to assisted breathing and subsequently achieves unassisted breathing to day 28, VFDs will be counted from the end of the last period of assisted breathing to day 28. A period of assisted breathing lasting less than 24 hours and for the purpose of a surgical procedure will not count against the VFD calculation. If a patient was receiving assisted breathing at day 27 or dies prior to day 28, VFDs will be zero. Patients transferred to another hospital or other health care facility will be followed to day 28 to assess this endpoint.

Time to extubation will be counted from time of study drug administration to extubation.

Duration of ventilation will be counted from time of study drug administration to being successfully free from assisted breathing.

Duration of critical care and hospital stay will be counted from time of study drug administration to discharge.

## **12.3 Sampling Procedures for Exploratory Outcomes**

### **Blood and Urine Sampling**

Blood samples (where possible) will be collected as follows by trained study staff and processed according to sample processing guidelines: (if measurements for translational studies cannot be collected this will not be recorded as a protocol deviation)

Baseline – up to 40ml plus additional 20ml for monocyte or neutrophil isolation

Day 4 - up to 40ml plus additional 20ml for monocyte or neutrophil isolation

Day 7 – up to 25 ml

Day 14 – up to 25 ml

Day 28 – 5ml

Year 1 – 10ml

Year 2 – 10ml

Blood samples at year 1 and 2 will be collected where possible

Urine samples (where possible) will be collected as follows by trained study staff and processed according to sample processing guidelines:

Baseline – 10ml  
Day 4 – 10ml  
Day 7 – 10ml  
Day 14 – 10ml

### Bronchoscopy and BAL

Bronchoscopy and BAL will be undertaken and BAL fluid processed as previously described [70,71]. In keeping with standard recommendations, patients who are receiving more than 80% inspired oxygen or have a high positive end expiratory pressure (PEEP) of >10cm H2O will not undergo bronchoscopy and BAL. In addition, if the ICU consultant has any concerns regarding safety the procedure will not be undertaken and will not be recorded as a protocol deviation.

Participants will be closely monitored during and after bronchoscopy and BAL. Participants will receive sedation and analgesia (to prevent discomfort) as part of standard care. Patients will be pre-oxygenated with additional sedation/muscle relaxants if necessary before passing a flexible bronchoscope through the endotracheal or tracheostomy (if relevant) tube. The scope will usually be passed into the right middle lobe and wedged in either the medial or lateral segment. Three aliquots of 60ml normal saline will be instilled and aspirated under gentle suction. BAL fluid will be placed on ice and transported to the laboratory for further analysis.

Predefined stopping criteria are established and if oxygen saturation, as measured by pulse oximetry falls to <92% bronchoscopy and BAL will be stopped.

Samples will be managed according to the Sample Processing Guideline. In summary, samples will be labelled with the patient's unique Participant Study Number. After processing locally samples will be transferred to Queen's University Belfast (QUB). Samples will be stored at –70°C until analysis. Samples will be stored beyond study completion in Queen's University Belfast. As new scientific data become available we will be able to use this resource of stored samples to investigate if this new data is relevant to ARDS pending additional ethical approval if required.

### Translational studies

Measurements will include:

1. Systemic inflammatory responses will be assessed by the following:  
Plasma and serum inflammatory response biomarkers which may include but are not limited to measurement of plasma CRP, cytokines (including but not limited to TNF $\alpha$ , IL1 $\beta$ , IL6, IL8), lipocalins, proteases and antiproteases, adhesion and activation molecule expression (including but not limited to sICAM1), NETs, circulating miRNAs, extracellular vesicles, lipid mediators, RAGE ligands, and whole blood transcriptome will be undertaken. Specific cellular populations within the blood (using but not limited to cytopins and flow cytometry) and identification of transcriptome changes within these cell populations will be investigated.
2. Indices of pulmonary and systemic epithelial and endothelial function and injury will be assessed by the following:  
Plasma and serum biomarkers which may include but not be limited to measurement of RAGE, Ang I/II, SP-D, vWF, PCP3 as well as total protein, plasma albumin,  $\alpha$ 2-macroglobulin, and protein permeability (albumin: $\alpha$ 2-macroglobulin ratio) will be undertaken. Urinary albumin/creatinine ratio and makers of extracellular matrix degradation including but not limited to desmosine will also be measured.

3. Coagulation

Markers of coagulation which may include but not be limited to the following, will be measured: Thrombin-antithrombin (TAT), activated FVII-antithrombin complex, FXI-AT, FXII-AT, C3a, sC5b-9, tissue factor, protein C, thrombomodulin and plasminogen activator inhibitor1 and thromboelastogram (TEG). Platelets, d-dimer and fibrinogen will be measured.

4. Anti-HLA antibodies

Two Luminex® assays will be undertaken; an initial antibody screen with Luminex® multi-antigen beads to detect class I and class II MHC antibodies followed by a Luminex® single antigen bead assay to determine the specificity of any antibody detected. The study samples will be analysed in an NHS clinical laboratory. These will be measured on day 0 samples and samples taken at day 28.

Samples from subjects may also be tested on primary cultures of fresh human neutrophils, monocytes and macrophages as well as mesenchymal stromal cells to provide mechanistic insights. Measurements may include but will not be limited to the measurement of cell activation (shape change, MSC surface marker expression, CD11b surface expression, superoxide release), adhesion and transmigration, cytokine release and MMP production, rate of apoptosis and their ability to phagocytose.

Monocytes or neutrophils will be isolated from blood at baseline. Cells will be stimulated (as monocytes) or matured for 5-7 days to produce monocyte-derived macrophages (MDMs). Cells (monocytes or MDMs) will be stimulated with LPS or other inflammatory stimuli to identify mechanisms modulating inflammatory responses in these cells during ARDS. The effect of MSCs on cytokine production and their regulation will be measured by techniques including ELISA, multiplex, western blot, transcription factor assays and gene expression.

## 12.4 Follow Up Visits and Procedures

The CTU will collect mortality data at day 28 and day 90 (if discharged from hospital).

### Participant Follow-Up

After discharge from hospital, participant survival and significant medical events at 1 and 2 years post study drug administration will be determined either by telephone interview, review of medical notes or the electronic health care record by site staff. In addition contact with the GP or NHS Digital (if available in that region), will be undertaken centrally by CTU staff.

Where possible patients will have follow-up blood samples taken at 1 and 2 years post study drug administration. Patients will be contacted by a member of the trial team and arrangements will be made for attendance at a suitable healthcare facility to have samples taken.

After being informed of a participant's discharge, the CTU will send a note thanking them for their participation in the study and reminding them we will be back in contact for follow-up. Study participants will be asked to let the CTU know if they move house at any time after hospital discharge; NHS Digital will enable us to locate patients who move without informing the CTU.

## 13 DATA COLLECTION AND MANAGEMENT

### **13.1 Data Collection**

To ensure accurate, complete and reliable data are collected, the CTU will provide training to site staff in the format of investigator meetings and/or site initiation visits.

All data for an individual patient will be collected by the PI or designee and recorded in source documents/electronic CRF for the study. For routinely collected clinical data the NHS record will be the source document. Patient identification on the CRF will be through their unique participant study number, allocated at the time of enrolment. Data will be collected and recorded on the electronic CRF by the PI or designee as per the CRF submission guidelines.

If the participant is transferred to another hospital the PI or designated member of the site study team will liaise with the receiving hospital to ensure complete data capture as per CRF instruction. If this is not possible, the primary outcome must be collected as a minimum.

Data censorship for each trial participant will occur 90 days post study drug administration.

### **13.2 Data Management**

Following the entry of patient data into the study database, the data will be processed as per the CTU Standard Operating Procedures (SOPs) and the study specific Data Management Plan (DMP). Data queries will be generated electronically for site staff to clarify data or provide missing information. The designated site staff will be required to respond to these queries. All queries will be responded to/resolved within the study database and amended in the study database.

### **13.3 Data Quality**

The CTU will provide training to site staff on trial processes and procedures including CRF completion and data collection.

On-site monitoring visits during the trial will check the accuracy of entries on the electronic CRF against the source documents, the adherence to the protocol, procedures and Good Clinical Practice (GCP).

Quality control is implemented by the CTU in the form of Standard Operating Procedures (SOPs), which are defined to encompass aspects of the clinical data management process, and to ensure standardisation and adherence to International Conference of Harmonisation Good Clinical Practice (ICH-GCP) guidelines and regulatory requirements.

Data validation will be implemented and discrepancy reports will be generated following data entry to identify discrepancies such as out of range, inconsistencies or protocol deviations based on data validation checks programmed in the clinical trial database.

A Data Monitoring & Ethics Committee (DMEC) will be convened for the study to carry out reviews of the study data at staged intervals during the study.

## **14 STATISTICAL CONSIDERATIONS**

### **14.1 Sample Size**

The phase 1 trial will recruit up to 18 participants.

Although the primary focus of the phase 2 trial is safety, there is, however, power to detect a difference in physiological outcomes.

The sample size for the phase 2 REALIST trial is 60 patients with ARDS due to COVID-19 and 60 patients with ARDS not due to COVID-19 (30 in each of the ORBCEL-C and placebo groups). The recruitment, randomisation, treatment, outcome measurement and reporting, and follow-up processes will be as streamlined as possible.

Due to the clinical differences in patients with ARDS due to COVID-19 and other causes of ARDS, patients with ARDS due to COVID-19 and other causes of ARDS will be recruited as separate cohorts. This will also facilitate timely reporting of the results from each cohort.

The primary efficacy outcome measure will be the difference in oxygenation index (OI) between the ORBCEL-C and placebo treated groups at day 7. Based on our data from a recently completed clinical trial in ARDS, the mean (standard deviation; SD) OI at day 7 in patients with ARDS is 62(51)cmH2O/kPa [4]. To allow 1:1 recruitment (ORBCEL-C vs placebo) a sample size of 56 subjects will have 80% power at a two-tailed significance level of 0.05 using a two-sample t-test to detect a clinically significant difference of 39 cmH2O/kPa in OI between groups. In a previous phase 2 study of similar size, we have found that an intervention can demonstrate a change in OI of a similar magnitude confirming a treatment effect of this size can be achieved [4]. Although we anticipate few withdrawals or loss to follow-up we have allowed for this in the sample size calculation. In previous UK multicentre studies in the critically ill <3% withdrew consent or were lost to follow-up [4, 65] and on this basis a conservative drop-out rate of 5% has been estimated. Therefore a total of 60 evaluable patients who have received study drug (30 patients in the ORBCEL-C and 30 in the placebo group) will be recruited into each cohort.

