## 4 BACKGROUND AND RATIONALE

### 4.1 Acute Respiratory Distress Syndrome

Acute Respiratory Distress Syndrome (ARDS) is a common condition of acute hypoxemic respiratory failure resulting from disruption of the alveolar-capillary barrier, and a resultant inflammatory pulmonary oedema. It can occur in the critically ill in response to many insults including severe trauma, burns, infection, major surgery or neurological disorders. ARDS is a leading cause of death and disability in critically ill adults and children worldwide (1), with a hospital mortality of approximately 40% (1-3). UK data suggest that up to 20,000 cases of ARDS occur annually; 50% of these fall into the “moderate -severe” category of ARDS and have up to 40% mortality (2, 4). ARDS confers a considerable long-term illness and disability burden on the individual sufferer and on society. Only 50% of survivors are able to return to work 12 months after hospital discharge, while cognitive, psychologic, and physical morbidity persists for up to 5 years (5, 6).

ARDS has significant resource implications, prolonging intensive care unit (ICU) and hospital stay, and requiring rehabilitation in the community, all of which impact on NHS services. Patients with ARDS account for 10% of intensive care unit (ICU) admissions, and because they have a long average stay in ICU they use up to a quarter of ICU bed-days (7). The high incidence, mortality, long-term consequences and high economic costs make ARDS a major clinical problem. The estimated global annual cost of ARDS is \$613 million (USD). Within the NHS the estimated costs per patient up to 28 days are £22.5K and at 6 months are £30.5K (8).

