### 7.1 Primary Outcome Measure

The primary safety outcome is the incidence of serious adverse events (SAEs).

The primary efficacy outcome is oxygenation index (OI) at day 7.

OI is a physiological index of the severity of ARDS and measures both impaired oxygenation and the amount of mechanical ventilation delivered. OI is independently predictive of mortality in patients with ARDS (59, 60). We have chosen day 7 as we expect this time interval will minimise the competing effects of death and extubation, while allowing a sufficient time interval for a biological effect to occur.

OI is calculated as  $(\text{mean airway pressure (cm H}_2\text{O)} \times \text{FiO}_2 \times 100) \div \text{PaO}_2 \text{ (kPa)}$ . These simple measurements are easily and routinely collected as part of standard ventilator practice.

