### 7.2 Secondary Outcome Measures

The following clinical outcomes will also be assessed:

1. OI at days 4 and 14.
2. Physiological indices of ARDS, as measured by respiratory compliance (Crs), driving pressure and P/F ratio on days 4, 7 and 14.
3. Organ failure as measured by the sequential organ failure assessment (SOFA) score on days 4, 7 and 14.
4. Extubation and reintubation.
5. Ventilation free days at day 28.
6. Duration of ventilation.
7. Length of ICU and hospital stay.
8. 28-day and 90-day mortality.

Outcomes will be measured at baseline and daily up to day 14 or until the patient is discharged from ICU or the patient dies, and thereafter as necessary for the 28-day and 90-day mortality.

Patients will be followed up annually up to 2 years following study drug administration.

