#### 14.4 Missing Data

Every effort will be made to minimise missing baseline and outcome data in this trial. The level and pattern of the missing data in the baseline variables and outcomes will be established by forming appropriate tables and the likely causes of any missing data will be investigated. This information will be used to determine whether the level and type of missing data has the potential to introduce bias into the analysis results for the proposed statistical methods, or substantially reduce the precision of estimates related to treatment effects. If necessary, these issues will be dealt with using multiple imputation or Bayesian methods for missing data as appropriate.

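### The 80% power for day-7 oxygenation index allows for withdrawal and loss to follow-up but not for death or liberation from ventilation, after which the index has no value

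*Protocol*

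**What the plan says.** Section 14.1 states that "a sample size of 56 subjects will have 80% power" in each cohort, "to detect a clinically significant difference of 39 cmH"2O/kPa, with a day-7 mean (SD) of 62 (51). It then notes that under 3% withdrew consent or were lost to follow-up in previous UK critical care studies, and "on this basis a conservative drop-out rate of 5% has been estimated". This gives 60 per cohort, 30 per arm. These 60 are called evaluable, a word the sentence ties to having received study drug, not to having a day-7 OI.

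Section 7.1 calculates OI from mean airway pressure, FiO2 and PaO2. On timing it says "We have chosen day 7 as we expect this time interval will minimise the competing effects of death and extubation", without a rate for either event. Section 7.2 has outcomes measured "daily up to day 14 or until the patient is discharged from ICU or the patient dies".

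Section 14.3 lists t-tests, analysis of covariance, transformations and non-parametric equivalents for continuous outcomes. Section 14.4 has the level, pattern and likely causes of missing data examined first and then, if necessary, allows "multiple imputation or Bayesian methods for missing data as appropriate".

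**The concern.** A patient who has died or come off the ventilator by day 7 has no OI to record. This differs from withdrawal or loss to follow-up: the value does not exist, and the reason is itself an outcome of the disease and possibly of the treatment. The protocol recognises this when it chooses day 7, but gives it no place in the loss allowance. Section 4.1 cites "a hospital mortality of approximately 40" per cent. That is not a day-7 figure, but it makes an allowance of zero hard to defend without data.

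Two things are at stake. First, the power statement may be more favourable than the number of measured values will support. Second, if the comparison uses only patients with an observed OI, the arms are compared within groups selected by what happened after randomisation. A treatment that speeds liberation would remove its most improved patients from its own arm, and one that hastens death in the sickest would remove its worst. Benefit or harm on OI could then be masked.

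**Working it through.** **Inputs (section 14.1).** Difference 39, SD 51, two-sided alpha 0.05, two-sample t-test, 1:1 allocation, 60 recruited per cohort, 5% allowance.

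**Step 1: reproduce the stated size.** Standardised difference d = 39/51 = 0.765. Exact (noncentral t) power reaches 80% at 27.84 per arm, so 28 per arm and 56 in total; power at 28 per arm is 80.2%. Inflation gives 56/(1 − 0.05) = 58.9, so 59, and 60 to keep the arms equal. The stated figures are correct on their inputs.

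**Step 2: the margin.** 60 − 56 = 4 patients, or 4/60 = 6.7% of a cohort. With 55 measured (27 and 28 per arm), power is 79.5%. So a fifth patient without a day-7 OI, for any reason, takes the unadjusted test below 80%.

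**Step 3: power over a range.** The documents give no share dead or liberated by day 7, so the shares below are assumptions. Measured patients per arm = 30 × (1 − share). The fourth column solves the same power equation for the difference. The last column is 56/(1 − share), rounded up.

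| Share without day-7 OI | Measured per arm | Power for 39 | Difference detectable with 80% power | Recruits needed to keep 56 measured |
|---|---|---|---|---|
| 5% | 28.5 | 81% | 39 | 59 |
| 10% | 27 | 79% | 40 | 63 |
| 20% | 24 | 74% | 42 | 70 |
| 30% | 21 | 68% | 45 | 80 |
| 40% | 18 | 61% | 49 | 94 |
| 50% | 15 | 53% | 54 | 112 |

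**Step 4: what covariate adjustment could recover.** Section 12.2 collects baseline OI and section 14.3 lists analysis of covariance. With baseline correlation r, the residual SD is 51 × √(1 − r²). The documents do not give r, so it is an assumption.

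- r = 0.5: SD = 51 × 0.866 = 44.2 and d = 39/44.2 = 0.883. Power is 85% at 20% loss (24 per arm) and about 80% at 30% loss (21 per arm).
- r = 0.4: SD = 51 × 0.917 = 46.7 and d = 0.834. Power is 81% at 20% loss.

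These figures ignore the one degree of freedom spent on the covariate. They address precision only; adjustment for baseline does not undo selection by death or liberation.

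**Step 5: the word 'evaluable'.** If all 60 had a day-7 OI, power at 30 per arm would be 83.0%. The sentence defines the 60 by receipt of study drug, so it does not guarantee this.

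**The case against.** The strongest reply has four parts.

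- **No rate is given.** Nothing in the protocol says how many patients die or are liberated by day 7, and the 40% is hospital mortality. Day 7 was chosen to keep these events few. A reader might infer that the stated 80% will not be reached, but the documents do not show that. This stands, and only the conditional statement is supported.
- **No complete-case t-test is fixed.** A reader might infer that the trial will compare only patients with an observed OI. Section 14.3 leaves other methods open and promises a detailed statistical analysis plan before any analysis, which may say how these patients are handled. Nor does section 14.4 direct anyone to impute an OI after death. This stands as well, so the selection argument is about what such an analysis would do.
- **Covariate adjustment could restore power.** This stands in part: step 4 shows how much, under assumed correlations.
- **Excess early deaths would not go unseen.** The DMEC is to meet monthly at first and receives all-cause deaths. Mortality and extubation are outcomes in their own right, and ventilator-free days are zero for a patient who dies before day 28. This stands for the safety of the trial. It does not repair the reading of the day-7 OI result.

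Deferring to the analysis plan does not answer the sample size point. The loss allowance and its basis are stated in section 14.1, and that section leaves out two events that section 7.1 names.

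**Conclusion.** The concern holds in conditional form. Section 14.1 gives 80% power after an allowance for withdrawal and loss to follow-up only, for an outcome that does not exist after death or off the ventilator. Without covariate adjustment, the 80% requires at least 56 of 60 patients per cohort to have a day-7 OI. If 20% to 50% do not, power is 74% to 53% and the difference detectable with 80% power is 42 to 54 cmH2O/kPa, against the planned 39. Those shares are assumptions, and adjustment for baseline OI would soften the loss by an amount that depends on an unknown correlation.

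A comparison restricted to observed values would, in addition, be between groups selected after randomisation. The documents do not establish that this analysis will be used, or that the answer would have the wrong sign. The point should be fixed, but it is not a fatal defect.

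**What to change.** **Section 14.1**
- State that the 80% power holds, without covariate adjustment, only if at least 56 of 60 patients per cohort have a day-7 OI.
- Give the expected share dead or liberated from ventilation by day 7, with its source. Failing that, give power over a range of 5% to 50%, as in the table.
- Define 'evaluable' as having a day-7 OI, or drop the word. With that definition, enrolling 60 evaluable patients would mean recruiting more than 60.

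**Sections 14.3 and 14.4**
- State that OI will not be imputed after death.
- Report counts of death and of liberation from ventilation by day 7, by arm, beside the OI result.
- Add a supportive day-7 analysis of all treated patients that ranks death worst and alive and off the ventilator best, with ventilated patients ordered by OI between them.

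Whether that ranking should replace OI as the primary efficacy outcome is the sponsor's choice. It would include every treated patient whose day-7 state is known, but would give up a result in cmH2O/kPa and need its own sample size.

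The cost is a less favourable power statement and one extra analysis. Death, extubation, end of ventilation and daily ventilator and blood gas values are already collected under section 12.2, so no new data are needed.
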